### Randomization

Women meeting the inclusion criteria and for whom we have received from the gynecologists a phone number and a signed consent form agreeing to be contacted are included in the study and randomized with an allocation of 1:1. The randomization sequence uses a computer-generated random number list per region, since policies for follow-ups and treatment vary slightly across the regions. Randomization is undertaken by a third person, after which the project physician contacts women randomized to the intervention group.

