### Outcome measures

#### Primary endpoint

The primary endpoint is the relative rate of CIN2 regression between women in the intervention group and women in the control group. Regression is defined as having a diagnosis < CIN2 in the follow-up biopsy. As all women have CIN2 at entry, having less than CIN2 at follow-up entails a decreased risk of conization, and the woman will be referred back to her general practitioner for less frequent follow-ups according to national guidelines [6]. This outcome is, therefore, highly desirable. Another primary endpoint is the relative rate of CIN2 regression between women who consented to condom use and women in the control group. The regression rate in women who did not consent to condom use will be used to control for a possible selection bias. Regression rates will be reported by age.

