### Power calculation

Based on the literature [16, 17], we expect the regression rate in non-condom users to be around 22%, and regression in condom users to be 2.5 times larger. We expect the rate of condom use to be 60% in the intervention group, which gives an expected relative risk of 2.0 for the intervention group compared to the control group. With a power of 95% and a 0.05 significance level, we would need 140 women in each group.

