### Data analysis plan

The relative regression rate (RRR) for CIN2 in the intention-to-treat analysis will be calculated as$$ \mathrm{RRR}=\frac{\left(\mathrm{number}<\mathrm{CIN}2\ \mathrm{at}\ \mathrm{follow}\hbox{-} \mathrm{up}\ \mathrm{in}\ \mathrm{in}\mathrm{tervention}\ \mathrm{group}\right)/\left(\mathrm{all}\ \mathrm{women}\ \mathrm{in}\ \mathrm{in}\mathrm{tervention}\ \mathrm{group}\right)}{\left(\mathrm{number}<\mathrm{CIN}2\ \mathrm{at}\ \mathrm{follow}\hbox{-} \mathrm{up}\ \mathrm{in}\ \mathrm{control}\ \mathrm{group}\right)/\left(\mathrm{all}\ \mathrm{women}\ \mathrm{in}\ \mathrm{control}\ \mathrm{group}\right)}. $$

The relative HPV-clearance rate (RCR) is calculated as$$ {\displaystyle \begin{array}{l}\mathrm{RCR}=\\ {}\frac{\left(1-\mathrm{number}\ \mathrm{HR}\hbox{-} \mathrm{HPV}+\mathrm{at}\ \mathrm{follow}\hbox{-} \mathrm{up}\ \mathrm{in}\ \mathrm{in}\mathrm{tervention}\ \mathrm{group}\right)/\left(\mathrm{number}\ \mathrm{HR}\hbox{-} \mathrm{HPV}+\mathrm{at}\ \mathrm{baseline}\ \mathrm{in}\ \mathrm{in}\mathrm{tervention}\ \mathrm{group}\right)}{\left(1-\mathrm{number}\ \mathrm{HR}\hbox{-} \mathrm{HPV}+\mathrm{at}\ \mathrm{follow}\hbox{-} \mathrm{up}\ \mathrm{in}\ \mathrm{control}\ \mathrm{group}\right)/\left(\mathrm{number}\ \mathrm{HR}\hbox{-} \mathrm{HPV}+\mathrm{at}\ \mathrm{baseline}\ \mathrm{in}\ \mathrm{control}\ \mathrm{group}\right)}.\end{array}} $$

These calculations are possible because we have a closed population, in which all women recruited are followed up for the entire observation period. Logistic regression will be used to analyze the questionnaire data as predictors of outcomes. SAS version 9.4 will be used for the analysis.

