### Data sources

From the gynecologists, we will receive the name, date of birth, and phone number of women who have consented to be contacted. Every second week, we will receive a list from the pathology register [19] with new CIN2 diagnoses. Sample results from the follow-up visits as well as HPV status at baseline and follow-up will be retrieved from the pathology register. Data on adherence to condom use will be obtained from the questionnaires. All data will be linked via the women’s unique personal identification number. The Danish Data Inspective Agency has approved the handling and storage of data (SUND-2016-21). All study-related material will be stored safely. Personal information on the participants is stored in secure computer systems.

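### The primary relative regression rate uses neither age nor region, although both are known for every randomised woman; adjusting would be a free efficiency gain, not the repair of an error

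*Protocol article*

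**What the plan says.** Four parts of the protocol article bear on this.

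- **Data analysis plan.** The formula is introduced with "The relative regression rate (RRR) for CIN2 in the intention-to-treat analysis will be calculated as" and is the proportion with less than CIN2 in the intervention group over the same proportion in the control group, with all women of each group in the denominators. It has no covariate and no stratum. The only regression model named is logistic regression, and it is for questionnaire data.
- **Primary endpoint.** Age appears in one sentence: "Regression rates will be reported by age".
- **Data sources.** "From the gynecologists, we will receive the name, date of birth, and phone number of women who have consented to be contacted". Under Randomization, a signed consent to be contacted is a condition for entry, so age is known in both arms.
- **Randomization.** "The randomization sequence uses a computer-generated random number list per region". The stated reason is that follow-up and treatment policies differ slightly between regions. Age is not a stratification factor.

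**The concern.** Few baseline values are certain to be available for both arms. Control women are not contacted, and the questionnaire goes only to women who agreed to use condoms. HPV16 is the one baseline factor that the article links to regression, but the Intervention group section describes HPV testing for participating women only, so it may not be usable across arms. Age and region are therefore the practical adjustment set.

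The plan shows an interest in age by breaking regression down by it, and an interest in region by randomising within it, yet the primary estimate uses neither. If either is related to regression, the crude ratio carries variation that a model could remove. By-age rates do not do this: they leave the overall RRR unchanged and do not estimate whether the effect of the advice varies with age.

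At stake is some width of the confidence interval and some robustness to an unlucky age split. The validity of the comparison is not at stake.

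**Working it through.** **Step 1. The plan's own figure.** The inputs, all from Power calculation, are 22% regression without condoms, a 2.5-fold rate in users, and 60% uptake in the intervention arm. The result given there is: "With a power of 95% and a 0.05 significance level, we would need 140 women in each group".

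- Diluted relative risk: 0.6 × 2.5 + 0.4 × 1 = 1.9, so 22% × 1.9 = 41.8%. The article rounds this to 2.0.
- Two proportions, pooled variance under the null, two-sided 0.05 (sidedness is not stated), power 95%: n = [1.960 × √(2 × 0.319 × 0.681) + 1.645 × √(0.22 × 0.78 + 0.418 × 0.582)]² / 0.198² = 141.03, which rounds up to 142 per group. Power at 140 per group is 94.9%.
- With the rounded 2.0 (22% against 44%) the same formula gives 116.

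So 140 per group follows, within rounding, from 1.9. It rests on crude proportions and does not depend on any age adjustment.

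**Step 2. What age adjustment would gain.** The article gives no age effect, so a range is assumed. In a simulation of 6,000 trials per scenario, each trial had 140 women per arm and true regression of 22% and 44% (the stated relative risk of 2.0). Age was standardised and normally distributed, with the same odds ratio per standard deviation (SD) in both arms. The crude RRR was compared with a marginal RRR standardised from a logistic model with arm and age.

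| Assumed odds ratio per SD of age | SD of ln(RRR), crude | SD of ln(RRR), adjusted | Variance ratio | Women per arm, 140 × (1 − ratio) |
|---|---|---|---|---|
| 1.0 | 0.1877 | 0.1878 | 1.002 | 0 |
| 1.25 | 0.1887 | 0.1880 | 0.993 | 1 |
| 1.5 | 0.1911 | 0.1883 | 0.971 | 4 |
| 2.0 | 0.1868 | 0.1796 | 0.924 | 11 |
| 2.5 | 0.1869 | 0.1756 | 0.883 | 16 |

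As a check on the first row, the usual formula gives √(0.78/(140 × 0.22) + 0.56/(140 × 0.44)) = 0.186.

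Mean ln(RRR) was about 0.70 for both estimators in every row (ln 2 = 0.69). Adjustment therefore keeps the same target, and the crude ratio is not biased. The first row also shows that adjusting for a non-prognostic age costs practically nothing.

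In terms of the interval, at the strongest assumed effect and an RRR of 2.0, the 95% limits are 2 × exp(±1.96 × 0.1869) = 1.39 to 2.88 crude, and 2 × exp(±1.96 × 0.1756) = 1.42 to 2.82 adjusted.

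**Step 3. What a chance age imbalance does in one trial.** The standard error of the difference in mean age between arms is √(2/140) = 0.12 SD.

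| Assumed odds ratio per SD | Factor on crude RRR, imbalance of 1 SE | Imbalance of 1.96 SE |
|---|---|---|
| 1.25 | 1.02 | 1.03 |
| 1.5 | 1.03 | 1.07 |
| 2.0 | 1.05 | 1.11 |
| 2.5 | 1.07 | 1.13 |

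The last column is reached in one randomisation in 20, counting both directions, and in one in 40 in the direction that inflates the RRR.

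**Step 4. Cross-check with two age halves.** Let regression differ by a gap g between younger and older women, with average regression of 32% (midpoint of 22% and 41.8%). Then R² = (g/2)² / (0.32 × 0.68), and the gain in women is 280 × R² / (1 − R²).

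- g = 5 points: R² = 0.3%, about 1 woman of 280.
- g = 10 points: R² = 1.1%, about 3.
- g = 20 points: R² = 4.6%, about 13.
- g = 30 points: R² = 10.3%, about 32.

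This is the same order as Step 2.

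**Step 5. Region.** The article gives no regression rates by region, so no figure is offered. The argument for including it is that the lists are drawn up by region and that the article gives a reason for doing so.

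**The case against.** The strongest case on the other side is that this is a preference. A crude risk ratio in a 1:1 randomised trial is valid, reporting rates by age is compatible with it, and no statement in the article is false or contradictory. That stands, and it sets the weight of the point.

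It can also be said that covariate adjustment belongs in the statistical analysis plan, which is not shown. That stands for supporting analyses: the article does not exclude them. It does not dispose of the point, because the article writes out the primary formula, and that formula is crude.

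Three stronger readings are tempting, and the article does not support them.

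- *That the protocol treats age as a predictor of regression.* It only promises rates by age. The one baseline factor it links to regression is HPV16. Any gain from age is therefore conditional.
- *That chance age imbalance biases the result.* The shifts in Step 3 are part of the sampling variation that a valid interval for the crude ratio already covers. They are also small beside a planned RRR of 1.9 to 2.0.
- *That by-age reporting is a plan for subgroup claims.* The article names no age bands, no age-specific ratios and no claim that the effect differs by age.

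**Conclusion.** The point holds as an efficiency improvement. The stated primary RRR uses neither age nor region, both known for every randomised woman. The crude ratio remains valid, and the sample size and power under Power calculation are unaffected.

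The gain is nil if age is not prognostic, about 1% to 8% of the variance of ln(RRR) for odds ratios of 1.25 to 2.0 per SD of age, and about 12% at 2.5. These odds ratios are assumptions. The figures also rest on 140 women per arm, regression of 22% and 44%, and an age effect that is linear on the log-odds scale and equal in both arms. The contribution of region is not quantified. The change is worth making because it costs almost nothing, but the trial's conclusion does not depend on it.

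**What to change.** In the Data analysis plan, state that the intention-to-treat RRR is a marginal risk ratio, with its 95% confidence interval, from a prespecified model with arm, age as a continuous variable and region. Either logistic regression with standardisation or modified Poisson regression with robust variance will serve. Name one of them. Keep the present crude ratio as a sensitivity analysis. Because the trial is unblinded, fix this before follow-up diagnoses are compared between arms.

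Optionally, under Primary endpoint, accompany the by-age rates with a single arm-by-age interaction on the ratio scale and its confidence interval, labelled exploratory.

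The cost is a few sentences and a few lines of SAS. No new data are needed, and the effect measure remains a marginal risk ratio comparable with the planned RRR.

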#### Secondary endpoint

The secondary endpoint is clearance of HR-HPV for women who consented to condom use, based on the baseline sample and the follow-up sample. Clearance is defined as having a HR-HPV type at the time of CIN2 diagnosis that is not present at the follow-up. Previous studies have showed that having HPV16 will decrease the chance of regression of a CIN lesion [20]. Therefore, the initial HPV status and phenotypes might influence the regression rate of cervical lesions.

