Male condom use (or, simply, condom use) has been shown to confer considerable protection against HPV infection, though the protection is less perfect than for other sexually transmitted diseases [10, 11]. Furthermore, condom use has been hypothesized to improve the regression rate of cervical lesions [12]. Firstly, condom use may reduce HPV infection and reinfection, and thereby allow the immune system to repair a cervical lesion. Secondly, semen has an immunosuppressive effect, which is considered an advantage in the reproductive process, but when cervical lesions have developed, the absence of semen could benefit the cellular immune response [13–15]. Lastly, the latex used for condoms is a foreign material that could enhance the cellular immune response and contribute to regression of a cervical lesion.

Two small studies found an increased regression rate of cervical lesions when condoms were used in the short term [16, 17], but this finding was not supported by a small questionnaire-based study [18]. The studies were too small to provide conclusive evidence, and condom use cannot, therefore, be included in the current guidelines for the management of CIN.

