### Strengths and limitations

A strength of this study is its design as a public health randomized controlled trial embedded in the routine treatment and follow-up program for women with cervical lesions. This gives us two groups of women who are comparable except for the intervention. It is, furthermore, a strength to have three regions included. In Denmark, health care is paid for by the government and is free of charge [26], but there are minor regional variations in clinical procedures, and recruiting participants from three regions ensures that there is a representative sample of women.

The number of drop-outs is a limitation in this project. We do not receive consent to be contacted from all women attending a gynecologist, some women in the intervention group cannot be reached by phone or text message, and some women do not want to participate. Participating women may, therefore, be a selected group. Furthermore, adherence to condom use is inevitably self-reported. This information is collected from questionnaires at the end of the project, so there could be some recall bias. A punch biopsy may alter the HPV infection, and the disappearance of a type-specific HPV infection can be caused either by a biopsy or by an actual clearance. As the study is embedded in the clinical setting, we are not able to validate histology diagnoses or perform p16 staining. However, as the routine diagnostic procedures are used for both the intervention group and the control group, any possible misclassification will affect the two groups equally.

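### HR-HPV clearance is defined by type, but its formula counts women positive for any HR type, so new infections are scored against clearance

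*Protocol article*

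**What the plan says.** The Secondary endpoint section of the protocol article sets the population and the data: "The secondary endpoint is clearance of HR-HPV for women who consented to condom use, based on the baseline sample and the follow-up sample". It then gives the rule: "Clearance is defined as having a HR-HPV type at the time of CIN2 diagnosis that is not present at the follow-up". The rule concerns a particular type in a particular woman. The Strengths and limitations section keeps to that idea when it warns that "the disappearance of a type-specific HPV infection can be caused either by a biopsy or by an actual clearance".

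The Data analysis plan then prints a formula for a relative clearance rate (RCR), intervention over control. Within each group it uses two counts: women HR-HPV positive at follow-up, and women HR-HPV positive at baseline. Neither count refers to type, and the follow-up count is not restricted to women who were positive at baseline. The stated justification is: "These calculations are possible because we have a closed population, in which all women recruited are followed up for the entire observation period".

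**The concern.** Two sections fix the same endpoint by rules that can disagree on the same data. Under the formula, a woman who loses her baseline type but acquires another HR type is still positive and so not cleared. A woman negative at baseline and positive at follow-up adds to the follow-up count without being in the baseline count, and so offsets another woman's genuine clearance.

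This matters here because new infection is part of the proposed mechanism. The Background says that "condom use may reduce HPV infection and reinfection, and thereby allow the immune system to repair a cervical lesion". A statistic meant to show clearance would then partly show prevention of new infection.

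A second, independent weakness lies in the definition. Read literally, it is met when any one baseline type disappears, so a woman with two types who loses one is cleared while the other persists. The same section notes that HPV16 makes regression less likely, so which type persists is not a trivial matter.

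**Working it through.** **Plan's own figure.** The article states no HPV prevalence, clearance or acquisition rate, so there is nothing to reproduce. The 140 per group concerns CIN2 regression and has no bearing here.

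**Notation for one group.** Divide the *B* women HR-HPV positive at baseline into:
- *K*: keep all baseline types
- *P*: lose some baseline types and keep at least one
- *S*: lose all baseline types and acquire a new HR type
- *N*: HR-HPV negative at follow-up

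So *B* = *K* + *P* + *S* + *N*. Let *A* be the number of baseline-negative women who are positive at follow-up.

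**The rules.**
- Definition read literally (at least one baseline type lost): (*N* + *S* + *P*)/*B*
- All baseline types lost: (*N* + *S*)/*B*
- Formula with the bracket corrected: 1 − (*K* + *P* + *S* + *A*)/*B* = (*N* − *A*)/*B*

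The formula falls below the all-types-lost rule by (*S* + *A*)/*B*, which consists only of new infections. It falls below the literal definition by (*P* + *S* + *A*)/*B*. The formula puts *P* among the positives, so partial loss is never clearance under it.

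**Assumed cohort (all inputs hypothetical).** There are 84 women, 75 positive and 9 negative at baseline. Of the 75, 30 lose all baseline types and 45 stay positive. Of the 30, 5 acquire a new type (*S* = 5, *N* = 25). Of the 9, 2 become positive (*A* = 2).
- All baseline types lost: 30/75 = 40.0%
- Follow-up positives: 45 + 5 + 2 = 52
- Formula: 1 − 52/75 = 23/75 = 30.7%
- Gap: (5 + 2)/75 = 9.3 percentage points

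**Range, with the same 30 of 75 losing all baseline types.**
- *S* = 0, *A* = 0: 1 − 45/75 = 40.0%, gap 0
- *S* = 0, *A* = 2: 1 − 47/75 = 37.3%, gap 2.7 points
- *S* = 5, *A* = 0: 1 − 50/75 = 33.3%, gap 6.7 points
- *S* = 10, *A* = 4: 1 − 59/75 = 21.3%, gap 18.7 points

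The 40% equals the literal definition only if none of the 45 has partial loss. If 10 of them did, the literal definition would give (30 + 10)/75 = 53.3%.

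**Two arms, only if control samples are also typed (hypothetical).** Take 100 women per arm, 85 positive at baseline. Intervention: *K* = 40, *P* = 10, *S* = 5, *N* = 30, *A* = 5. Control: *K* = 40, *P* = 10, *S* = 10, *N* = 25, *A* = 8.
- All baseline types lost: 35/85 = 41.2% in both arms, ratio 1.00
- At least one lost: 45/85 = 52.9% in both arms, ratio 1.00
- Formula: 1 − 60/85 = 29.4% against 1 − 68/85 = 20.0%, RCR = 1.47

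With equal type-specific clearance, the 1.47 comes entirely from the assumed difference in new infections.

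**Bracket.** As printed, each term is (1 − count)/count, for example (1 − 52)/75 = −0.68. That is a separate slip, and correcting it leaves the mismatch in place.

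**The case against.** The best defence is that a condensed article uses HR-HPV positive at follow-up as shorthand governed by the definition given earlier. The endpoint is based on paired samples, the Data sources section links all records by personal identification number, and the limitations also speak of type-specific infection. On this view the intended concept is consistent and only the label in the formula is loose. It is fair that the intent is probably type-specific and that the data could support it. But an analyst following the printed formula would not obtain that quantity. Linkage makes the right calculation possible without putting it into the formula. A closed population does not help either, because women in a closed cohort can still acquire infections.

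It is also fair that the handling of several types in one woman is often left to an analysis plan. That part is an ambiguity in the definition, and weaker than the conflict between the sections.

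Two stronger readings are tempting. A reader might infer that the formula itself lets partial loss of types pass as clearance. It does the reverse: a woman who keeps any HR type is still positive and not cleared. A reader might also infer that the comparison between arms is biased. The documents do not establish that. The endpoint is limited to women who consented to condom use, the Intervention group section describes HPV testing for participating women, and the Control group section mentions only the biopsy result. The Data sources section mentions HPV status without naming a group. Within one arm, new infections lower the reported clearance but cannot create a difference between arms.

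**Conclusion.** The point stands as a contradiction between two sections on the only secondary endpoint. The definition is type-specific. The formula, with its bracket corrected, is a net change in any-type positivity that counts type swaps and new infections against clearance. It can never exceed the all-types-lost rate, and it falls short by the number of new infections of these two kinds divided by the baseline positives.

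The size cannot be established from the documents. The 31% against 40% rests on invented inputs and compares the formula with the all-types-lost rule. With few new types over about 6 months the gap could be small, and with none it is zero. The partial-loss problem belongs to the definition alone. The RCR of 1.47 shows what could happen if control HPV data exist and acquisition differs by arm; it does not predict a distortion. The CIN2 regression analyses are unaffected. The matter should be corrected, but it does not threaten the trial's main conclusion.

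**What to change.** State one woman-level rule in both the Secondary endpoint section and the Data analysis plan:
- **Denominator:** women with at least one HR type at baseline and a valid follow-up result.
- **Cleared:** none of the woman's baseline HR types is detected at follow-up.
- **Acquisition:** HR types that are new at follow-up, reported separately and not netted against clearance.

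Rewrite the formula as the number cleared over this denominator, which also removes the bracket problem. State whether control-group HPV results will be available. If they will not, report a clearance proportion in consenting women and no ratio.

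The cost is wording in two sections. The stated definition already requires type-level results, so no new testing follows from the rule for women already due to be typed. The rule should be settled before the HPV data are analyzed, so that the choice between the two versions does not follow the results.
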